### NIHR associate PI scheme

Meso-ORIGINS is enrolled on the NIHR Associate Principal Investigator Scheme, providing opportunities for early career researchers, with eight individuals involved to date.

The sample size estimate for arm B is 300, which is expected to generate at least 109 PM cases (one-sided 95% PI (109,+ve Inf)) based on a study by Tsim *et al* in which 69/155 (44.5%) participants with asbestos exposure and a clinical suspicion of PM had diagnosis confirmed at thoracoscopy.^23^ The sample size of arm B was increased from an original arbitrary estimate of 39 and subsequent increases to 120 and 250 following encouraging early recruitment. These changes followed publication of a study by Zhang *et al,*^18^ which reported highly complex exomic intratumour heterogeneity (ITH) based on 90 multiregion pleural biopsies collected from 22 PM patients and increased downstream requirements for the tissue and data being generated. The larger sample size also afforded an opportunity to test the diagnostic utility of an exhaled breath classifier for PM.^19^ An interim review of recruitment in March 2025 revealed 181 arm B recruits, recruited over 33 months, with a crude average of 5.5 cases/month. We conservatively predicted recruitment of 7 cases/month over the remaining recruitment period (April 2025 to August 2026), translating into an additional 119 recruits and a total of 300 cases by study end. The larger number of confirmed PM cases (n=109) predicted from this cohort will generate an estimated 436 multiregion PM biopsies (assuming four biopsies/case), increasing the pool of samples for ITH assessment by 7.6-fold. We predict collection of exhaled breath in 70 of 119 (around 60%) additional arm B participants recruited. Assuming 90% sensitivity and 80% specificity of the final classifier, 44.5% prevalence of PM and a 5% type I error rate, 70 cases will deliver precision in the final estimates of sensitivity and specificity not exceeding 11%.

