#### Secondary endpoint analyses

A classification model for PM evolution will be generated using the XGBoost tree boosting system, where SHAP values will be used to evaluate the contribution of each feature to individual predictions. Candidate features will include clinical variables and those derived from blood biomarker analyses (eg, proteomics), exhaled breath VOCs and perfusion MRI. The performance of the developed model will be assessed using a Receiver Operator Characteristic curve. Any model developed will be subjected to subsequent validation in an independent data set. The number of participants in arm B with confirmed PM following thoracoscopy will be reported by simple descriptive statistics. The CI will be based on the Agresti-Coull approach.^24^ The downstream heterogeneity analyses will be performed by a Bioinformatics team within the CRUK Scotland Institute, Glasgow and reported separately. The performance of the PM diagnostic classifier will be analysed using 2×2 contingency tables and reported as sensitivity and specificity, with 95% CIs.

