Updated timelines to extend recruitment by 1 year with a recruitment end date of 31 August 2026 and new study end date of 31 August 2028.Addition of exhaled breath collection to arm B to address the new secondary objective ‘To determine the diagnostic performance of an exhaled breath diagnostic classifier for detection of PM prior to thoracoscopy’.Addition of 1-year remote follow-up in arm B (visit B4).Updated arm B target from 250 to 300 in response to updated study timelines.Retrieval of postmortem biopsies performed as part of routine care within arm A.Removal of remote consent option for RO participants, minimising numbers without germline blood samples for downstream genomic analyses.

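### Seventy breath samples give a 95% half-width of about 12.6% for specificity, not the stated 11% or less

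*Protocol article*

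**What the plan says.** The Sample size section of the protocol article projects the number of breath samples from expected arm B recruitment: "We predict collection of exhaled breath in 70 of 119 (around 60%) additional arm B participants recruited". It then sets the assumptions, "Assuming 90% sensitivity and 80% specificity of the final classifier, 44.5% prevalence of PM and a 5% type I error rate", and concludes that "70 cases will deliver precision in the final estimates of sensitivity and specificity not exceeding 11" per cent. It does not define precision, say whether the 5% is one-sided or two-sided, or name an interval method for this calculation.

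Under Secondary endpoint analyses, classifier performance is to be "reported as sensitivity and specificity, with 95% CIs".

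The Changes to protocol section shows that breath sampling in arm B came in with V.2.2: "Addition of exhaled breath collection to arm B to address the new secondary objective". No earlier arm B breath samples were planned that could be added to the 70.

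**The concern.** One bound of 11% is claimed for both accuracy measures. Specificity is estimated in participants without PM and is assumed to be 80%, where the binomial variance (0.16) is well above that at 90% (0.09). The non-PM group is only a little larger than the PM group, so its size does not make up for this. Specificity is therefore the limiting measure, and it is the one that fails.

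This sentence is the only quantitative justification in the article for the diagnostic accuracy objective, which has its own row in Table 1. A reader would expect a specificity interval narrower than the study can be expected to produce.

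**Working it through.** **Inputs** (all from Sample size, except the confidence level, which is from Secondary endpoint analyses): N = 70; prevalence 0.445; sensitivity 0.90; specificity 0.80; 5% error; 95% CIs reported.

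**Group sizes**
- PM: 70 × 0.445 = 31.15
- Non-PM: 70 × 0.555 = 38.85

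**Formula** (normal approximation): half-width = z × √(p(1 − p)/n)

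**Reproducing the stated 11%.** With a one-sided 5% multiplier, z = 1.645:
- Sensitivity: 1.645 × √(0.09/31.15) = 8.8%
- Specificity: 1.645 × √(0.16/38.85) = 10.6%

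Both are within 11%. But z = 1.645 on each side of the estimate gives a two-sided 90% interval.

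**At the level to be reported.** With z = 1.960:
- Sensitivity: 1.960 × √(0.09/31.15) = 10.5%
- Specificity: 1.960 × √(0.16/38.85) = 12.6%

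Whole numbers (31 and 39) give 10.6% and 12.6%.

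**Other interval methods, 95%, half of the total width**

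| Method | Sensitivity | Specificity |
|---|---|---|
| Wald | 10.5% | 12.6% |
| Wilson | 10.9% | 12.3% |
| Jeffreys | 10.5% | 12.3% |
| Agresti-Coull | 11.6% | 12.6% |
| Clopper-Pearson (exact) | 12.0% | 13.5% |

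Specificity exceeds 11% under every method. Sensitivity meets it under three of the five.

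**Other readings tried**
- *Rounding of the 60%:* 0.60 × 119 = 71.4 participants gives 12.5% for specificity.
- *Rounding of the 11%:* even a half-width just under 11.5% needs about 84 participants.
- *70 cases meaning 70 PM cases:* this gives 7.0% and 8.4%, but the 70 is defined as participants sampled out of 119, and a prevalence is then applied.
- *All 70 as the denominator for specificity:* this gives 9.4%, but it ignores the prevalence.
- *A different prevalence:* at 11% and 95%, sensitivity needs 1.960² × 0.09/0.11² = 28.6 PM participants and specificity needs 1.960² × 0.16/0.11² = 50.8 non-PM participants. Together that is 79.4, more than 70, so no prevalence lets 70 participants meet the bound for both (Wald).

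**Number needed at the stated prevalence:** 50.8/0.555 = 91.5, so about 92 breath samples.

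**The case against.** The strongest reply is that the 11% is not an arithmetic slip. The sidedness of the 5% is not stated, and a one-sided reading reproduces the figure under Wald, and also under Wilson (9.1% and 10.4%) and Agresti-Coull (9.6% and 10.6%). The same section uses a one-sided 95% prediction interval for the number of arm B PM cases, so one-sided reasoning is not foreign to it. This is a plausible origin, though an inference. It does not rescue the sentence. The prediction interval is labelled one-sided and the breath calculation is not, and the analysis section commits to 95% CIs. A reader will take the 5% and the 95% as matching.

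Three further points bear on weight, and they stand:
- The gap is small and concerns a secondary objective. The final report will show the actual interval.
- The 70 comes from projected recruitment, not from a precision target. Correcting the 11% therefore need not change the number sampled, and the 92 is only what an 11% bound would require.
- The 10.5% for sensitivity depends on the Wald formula, whose upper limit here is 90% + 10.5% = 100.5%. Under Agresti-Coull, the method the article names for its other proportions, sensitivity would also miss 11%, at 11.6%.

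It could also be said that naming an interval method belongs in the statistical analysis plan. That is fair, and its absence is not the complaint here. The complaint is that a stated number does not follow from its stated inputs at the stated reporting level.

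**Conclusion.** The concern holds. On the article's own inputs, the expected 95% half-width for specificity is 12.6% (12.3% to 13.5% across standard methods), against a stated maximum of 11%. The excess is about 1.6 percentage points under Wald. Sensitivity meets the bound under Wald, Wilson and Jeffreys, but not under Agresti-Coull or the exact method.

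This takes precision to mean the half-width of the 95% CI that will be reported, and takes the 70 to be PM and non-PM participants together. The first is the natural reading because the analysis section specifies 95% CIs; the second follows from the text. The primary endpoint and arm A are not affected.

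**What to change.** Replace the precision statement in Sample size with one along these lines:

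> With 70 breath samples and 44.5% prevalence (about 31 PM and 39 non-PM participants), the expected 95% CI half-widths are about 10.5% for sensitivity and 12.6% for specificity (normal approximation).

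Name the interval method and use the same one in the analysis. If Agresti-Coull is chosen, to match the other proportions in the article, the figures become about 11.6% and 12.6%.

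The alternative is to keep 11% and say that it refers to a 90% (one-sided 5%) interval under a named method. That leaves a mismatch with the planned 95% CIs, which would then have to be reconciled.

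The cost is one sentence and a slightly less favourable figure. Recruitment need not change. Only if the sponsor wants 11% for specificity at the 95% level would breath collection have to rise from 70 to about 92 (Wald).

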#### Patient and public involvement

The study management group includes a patient and public involvement (PPI) representative, who also contributed to protocol and patient-facing document design. They also contribute to ongoing reviews of study progress and emerging data.

### Statistical analysis plan

#### Primary endpoint analysis

The primary endpoint will be reported by simple descriptive statistics. The CI will be based on the Agresti-Coull approach.^24^

#### Secondary endpoint analyses

A classification model for PM evolution will be generated using the XGBoost tree boosting system, where SHAP values will be used to evaluate the contribution of each feature to individual predictions. Candidate features will include clinical variables and those derived from blood biomarker analyses (eg, proteomics), exhaled breath VOCs and perfusion MRI. The performance of the developed model will be assessed using a Receiver Operator Characteristic curve. Any model developed will be subjected to subsequent validation in an independent data set. The number of participants in arm B with confirmed PM following thoracoscopy will be reported by simple descriptive statistics. The CI will be based on the Agresti-Coull approach.^24^ The downstream heterogeneity analyses will be performed by a Bioinformatics team within the CRUK Scotland Institute, Glasgow and reported separately. The performance of the PM diagnostic classifier will be analysed using 2×2 contingency tables and reported as sensitivity and specificity, with 95% CIs.

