**Trial registration number:**

ISRCTN22929761.

WHAT IS ALREADY KNOWN ON THIS TOPICApproximately 15% of patients with benign asbestos-associated pleural effusion (also known as asbestos-associated non-specific pleuritis) are diagnosed with pleural mesothelioma (PM) within 2 years. This presents a unique opportunity for translational research focused on the development of novel therapies for use in early-stage or preinvasive disease.

WHAT THIS STUDY ADDSMesothelioma Observational study of Risk prediction and Generation of paired benign-meso tissue samples, Including a Nested MRI Substudy (Meso-ORIGINS) is the prospective tissue banking and risk prediction vehicle for the PREDICT-Meso International Accelerator network, funded by Cancer Research UK and its partners in Italy and Spain. The study is recruiting 600 patients across two arms, with Arm A focused on longitudinal follow-up of 300 asbestos-associated pleural inflammation (AAPI) patients, with repeat biopsy at PM evolution. Arm B is focused on multiregion pleural biopsy collection for evaluation of anatomical heterogeneity. The study is open at 32 sites in 27 UK cities.HOW THIS STUDY MIGHT AFFECT RESEARCH, PRACTICE OR POLICYThe tissue resources generated are being used for target identification, preclinical model development and the screening and validation of new therapies ready for human trials. Multiomic risk prediction in arm A, including blood proteomics, exhaled breath metabolomics and perfusion MRI will inform the eligibility criteria for future precision prevention trials. The samples collected, including pleural tissue, pleural effusion, blood, imaging, clinical data and derived omics, are being shared with the global PM research community via a REC-approved research tissue bank.

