### Study objectives and endpoints

Objectives and their associated endpoints are summarised in table 1.

**Table 1 T1:** Study objectives and associated endpoints

	Objective	Associated endpoint
Primary	To create a prospective cohort of patients with asbestos associated benign pleural disease of whom an estimated 38 will develop PM within 2 years	Number of patients in arm A diagnosed with PM at any point from study registration to completion of 2 years follow-up
Secondary	To generate a risk prediction model for evolution of PM within 2 years, based on serum proteomics, exhaled breath metabolomics and perfusion MRI	Results of a multiomic risk classifier based on radiomic, proteomic and metabolic measurements in patients at baseline in arm A
	To collect spatially distinct tumour biopsies from patients with PM, facilitating comprehensive characterisation of intrapatient tumour heterogeneity	Number of patients in arm B with histologically confirmed PM following thoracoscopy
	To determine the diagnostic performance of an exhaled breath diagnostic classifier for detection of PM prior to thoracoscopy	Sensitivity and specificity of an exhaled breath diagnostic classifier for histologically confirmed PM based on samples collected prior to thoracoscopy

PM, pleural mesothelioma.

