#### Baseline data collection

At baseline assessment in both study arms (visit A1 and B1), the data collected includes patient demographics, asbestos exposure history, presenting symptoms, performance status (PS), comorbidities and mode of presentation. Baseline blood and pleural fluid results can be extracted from routine clinical records if measured within 4 weeks of the study visit. Required data include full blood count, urea and electrolytes, C reactive protein, albumin, serum and effusion total protein, serum and effusion lactate dehydrogenase, plus effusion glucose, microbiology and cytology. Where these data are not available within this window, blood tests will be repeated at the same time as research bloods (see the section Translational bloods). In arm A, details of the biopsy on which the AAPI diagnosis was made will also be collected, including biopsy date, biopsy method and histological descriptors. Results of contrast-enhanced CT thorax should also be recorded at baseline, ideally acquired within 12 weeks of visit A1/B1.

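### For the arm A 2-year risk model the article names only SHAP values and a ROC curve, which cannot show what proteomics, breath or MRI add to routine data, or whether predicted risks are correct

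*Protocol article*

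**What the plan says.** All references are to the Protocol article.

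- **Objective and endpoint** (Study objectives and endpoints, Table 1). The secondary objective is "To generate a risk prediction model for evolution of PM within 2 years, based on serum proteomics, exhaled breath metabolomics and perfusion MRI". Its endpoint is "Results of a multiomic risk classifier based on radiomic, proteomic and metabolic measurements in patients at baseline in arm A".
- **Features** (Secondary endpoint analyses). "Candidate features will include clinical variables and those derived from blood biomarker analyses (eg, proteomics), exhaled breath VOCs and perfusion MRI". They enter one XGBoost model. CT is not named as a feature.
- **Contribution** (same section). "SHAP values will be used to evaluate the contribution of each feature to individual predictions".
- **Performance** (same section). "The performance of the developed model will be assessed using a Receiver Operator Characteristic curve".
- **Validation** (same section). "Any model developed will be subjected to subsequent validation in an independent data set". No metric or comparator is given for this step.
- **Intended use** (box on how the study might affect research, practice or policy). The multiomic work "will inform the eligibility criteria for future precision prevention trials".
- **CT** (Baseline data collection). "Results of contrast-enhanced CT thorax should also be recorded at baseline, ideally acquired within 12 weeks of visit A1/B1".

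Two other sections set questions about single platforms. Exhaled breath sampling says that previously reported breath markers will be tested for risk prediction in arm A. MRI sub-study in arm A gives the predictive value of reported perfusion markers as its objective.

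**The concern.** The measures named do not fit the questions asked.

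**Added value.** A SHAP value splits one prediction of a fitted model among its features. It does not say whether a feature improves prediction in new patients, because an overfitted model has SHAP values too. One ROC curve for the pooled model cannot separate what the platforms add from what routine data already supply. This matters here because Eligibility assessment, Arm A admits patients with persisting suspicion of PM and malignant-looking CT, even when rebiopsy is already planned. Routine data may already identify many of those who evolve.

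**Absolute risk.** A ROC curve depends only on the ranking of patients. A model for risk within a fixed 2-year horizon should also be checked for whether its predicted risks match those observed.

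At stake is crediting a costly platform with value that is noise or a restatement of routine findings, and passing miscalibrated risks to the designers of later trials.

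**Working it through.** **1. Events available (Sample size section).** Inputs: 36/257 evolutions in the feasibility cohort, 300 patients in arm A, at least 50 in the MRI substudy, 10% loss to follow-up.

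- Arm A: 300 × 0.9 × 36/257 = 37.8. The article states 38, so this reproduces.
- MRI: 50 × 0.9 × 36/257 = 6.3. The article states about 6, so this reproduces.

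Followed patients number 270 (38 events, 232 non-events) in arm A and 45 (6 and 39) in the MRI substudy.

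**2. Precision of an AUC (Hanley-McNeil).** With AUC *A*, *n1* events and *n0* non-events, let *u* = A/(2 − A) and *v* = 2A²/(1 + A). Then

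SE² = [A(1 − A) + (n1 − 1)(u − A²) + (n0 − 1)(v − A²)] / (n1 × n0).

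For A = 0.75 in arm A: [0.1875 + 37 × 0.0375 + 231 × 0.0804] / 8816 = 0.00228, so SE = 0.048 and the 95% half-width is 1.96 × 0.048 = 0.094.

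| Assumed AUC | Half-width, 38 events | Half-width, 6 events |
|---|---|---|
| 0.70 | 0.098 | 0.248 |
| 0.75 | 0.094 | 0.237 |
| 0.80 | 0.088 | 0.222 |

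These are for a single AUC. For a paired difference between two AUCs of equal SE and correlation *r*, the half-width is the tabled figure × √(2(1 − r)): the same at r = 0.5, narrower above it. The documents do not give *r*. They also do not say how many arm A patients will give breath, so no figure can be given for that platform.

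**3. Why a ROC curve cannot check risk.** Any increasing transformation of the predictions leaves the curve unchanged. Take a predicted risk of 36/257 = 14.0%, odds 36/221. If a model doubled every patient's odds, this risk would read 72/(72 + 221) = 24.6%, with an identical ROC curve.

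**4. Can calibration be checked at this size?** The 95% limits of observed/expected risk lie within a factor of exp(1.96 × √((1 − e/n)/e)) of the estimate, for *e* events in *n* patients. With 38/270 this is 1.34. With 6/45 it is 2.1. Overall calibration can be checked in arm A and only crudely in the MRI substudy.

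**5. Noise features (illustration only).** Effect sizes and numbers of noise features are assumptions, and all platform features are set to pure noise.

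*Gradient-boosted stumps, untuned* (100 rounds, rate 0.1): 270 patients, about 34 events, four true clinical predictors with log odds ratio 0.5 each; 40, 40 and 20 repeats; 5,000 new patients per repeat.

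| Noise features | 20 | 100 | 500 |
|---|---|---|---|
| Share of mean absolute SHAP on noise | 55% | 78% | 89% |
| Apparent (in-sample) AUC | 0.95 | 0.99 | 1.00 |
| AUC in new patients, full model | 0.65 | 0.60 | 0.56 |
| AUC in new patients, clinical only | 0.70 | 0.70 | 0.70 |
| Calibration slope in new patients (ideal 1) | 0.58 | 0.42 | 0.29 |

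*Penalised logistic model with linear SHAP*: 270 patients, two true clinical predictors, 300 repeats, 4,000 new patients each. Under a light penalty, 10, 20 and 40 noise features took 54%, 71% and 83% of SHAP. New-patient AUC was 0.69, 0.67 and 0.64, against 0.73 for clinical variables alone. Calibration slope was 0.65, 0.45 and 0.25. Under a heavier penalty the slope was 0.91 and 0.69 with 10 and 20 noise features.

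The two model types agree in direction. The size depends on the assumptions and on regularisation.

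**The case against.** The strongest reply is that this is a few sentences in a journal article. Nested comparisons and calibration statistics usually sit in an analysis plan, which is not shown. That stands in part: the benchmark and calibration are unstated here, not shown to be absent from the study. But the article does more than stay silent. It names the contribution and performance measures, and these suit its own objective badly.

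Several stronger readings are tempting, and the documents do not support them:

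- **That the model is never checked in new patients.** Independent validation is planned. A fall in AUC there would expose noise-driven performance, and calibration could be included. Validation by ROC curve alone, however, would still leave added value and calibration unknown.
- **That each platform's worth will be judged by SHAP.** The text uses SHAP for contributions to individual predictions. It is only the sole contribution measure named.
- **That eligibility will use an absolute-risk threshold.** None is stated, and the text also speaks of a classifier. The relevance of calibration rests on the 2-year risk prediction objective and is otherwise an inference.
- **That every arm A patient has a baseline CT result, or that CT is excluded from the model.** Recording is worded as expected, not guaranteed, and CT findings could count as clinical variables.
- **That the platforms are noise.** The breath and MRI markers have been reported before. The simulations show what could happen, not what will.

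It is also fair that one comparison of a full model with a benchmark does not fit the design, because MRI covers only a subset and breath only participating sites. The fix allows for this.

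**Conclusion.** The point holds in this limited form. For a 2-year risk model, the measures named in Secondary endpoint analyses cannot show whether proteomics, breath or MRI add to clinical and CT data, or whether predicted risks are correct. The later validation names nothing that would close the gap. This follows from what SHAP and a ROC curve measure and needs no simulation.

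The risk that an in-sample ROC curve and SHAP ranking flatter noise features is real at about 38 events, but its size is not established: the figures rest on assumed effects, pure-noise platforms and limited tuning. Arm A can support an overall calibration check and a moderately precise AUC. The MRI substudy cannot settle whether MRI adds anything. The change should be made; it does not call the study's design or its primary endpoint into question.

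**What to change.** In Secondary endpoint analyses:

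1. Fit the same modelling pipeline on clinical plus recorded baseline CT variables alone, as the benchmark.
2. For each platform, in the participants who have its data, report the paired out-of-sample (resampled) AUC difference, benchmark plus platform minus benchmark, with its 95% CI.
3. Report calibration intercept, slope and plot from the same out-of-sample predictions.
4. Name both checks as measures for the planned independent validation.
5. State that SHAP values are descriptive and are not evidence of added predictive value.
6. State that the MRI comparison is exploratory, with about 6 events and a single-AUC half-width of about 0.22 to 0.25.

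The cost is some wording and a little more analysis of data already being collected, with no extra patients or visits. The downside is that the claim for the omics platforms may come out less favourable.
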